#### Exploratory analysis

Analyses will also include an exploration of whether intervention effects differ across subpopulations based on sex (male vs. female), age (< 21 vs. 21 or older), and race/ethnicity. These exploratory moderation analyses may provide information that will allow for further refinement of the intervention as well as to help target the subpopulations for which it is most likely to be effective.

#### Power analysis

Power analyses were performed with power = 0.8 and alpha = 0.05 for small (f = 0.15), moderate (f = 0.25), and large (f = 0.45) effect sizes. With 100 participants, we are adequately powered to detect small (*n* = 62), moderate (*n* = 24), and large (*n* = 10) effects. We anticipate small to medium effects based on previous studies using PNF [42–44].

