## Methods/Design

### Trial design

This study is a 2-arm pilot RCT with 100 young adults who vape recruited through advertisements placed on social media. Participants will be randomized to the active intervention arm (*n* = 50) or to a waitlist-control arm (*n* = 50).

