### Control group

Participants randomized into the control condition will be instructed to complete the same online surveys (baseline, 2-,4-, and 8-week surveys) sent via email. Control participants will be given the option to access the intervention upon completion of their final assessment at 8-weeks. Along with participants in the experimental group, they will also receive a list of national and local resources for information about the effects of vaping in young people and help with reducing vaping behaviors after completion of the final assessment.

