### Data analysis plan

#### Primary analysis

Treatment effects of the intervention will be examined using within-subjects repeated measures analysis of variance (RM-ANOVA), which allows for investigations of changes in mean scores over 3 or more time points. Specifically, we will evaluate two models to examine whether there were changes in past 7-day vaping frequency and smoking susceptibility across 3 time points (2-, 4-, and 8-weeks post-randomization) among those who completed the intervention. Logistic regression will be used to examine point prevalence abstinence at our 3 follow-up timepoints. Next, RM-ANOVA will be used to determine whether any changes in past 7-day vaping frequency and smoking susceptibility are the result of the interaction between the condition and time. Past 7-day point prevalence abstinence will be compared between the treatment and control groups using logistic regression. To handle missing data, we will conduct an intent-to-treat (ITT) analysis in which those who were lost to follow-up will be marked as treatment failures.

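### The small-effect power claim made for 100 participants does not carry over to the completers-only primary models, which can include at most 50

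*Protocol article*

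**What the plan says.** The Power analysis section sets the criteria, "Power analyses were performed with power = 0.8 and alpha = 0.05", and considers "small (f = 0.15), moderate (f = 0.25), and large (f = 0.45) effect sizes". It then concludes: "With 100 participants, we are adequately powered to detect small (*n* = 62), moderate (*n* = 24), and large (*n* = 10) effects". It adds: "We anticipate small to medium effects based on previous studies using PNF". No analysis, number of measurements or correlation between measurements is named there.

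The Primary analysis section describes two steps for vaping frequency and smoking susceptibility. The first step is two within-subjects models "across 3 time points (2-, 4-, and 8-weeks post-randomization) among those who completed the intervention". The second step asks whether any changes "are the result of the interaction between the condition and time", which brings in both arms.

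Two other sections fix who can be a completer. Under Trial design: "Participants will be randomized to the active intervention arm (*n* = 50) or to a waitlist-control arm (*n* = 50"). Under Control group: "Control participants will be given the option to access the intervention upon completion of their final assessment at 8-weeks".

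**The concern.** The power sentence compares the required 62 with all 100 randomised participants, and nothing in it limits the claim to one of the two steps. Controls get access to the programme only after the week-8 survey, so none of them can be a completer during the period analysed. The first-step models therefore draw on the intervention arm alone. The intervention arm has 50 participants, below 62 even if everyone completes the programme and answers every survey.

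A small effect lies within the range that the authors expect. A reader who applies the power sentence to the completers-only models would take a non-significant time effect there as coming from a test with at least 80% power for f = 0.15, which those models do not have under the inputs that give n = 62.

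**Working it through.** **Inputs from the article.** Alpha 0.05, target power 0.80, f = 0.15 / 0.25 / 0.45, required n = 62 / 24 / 10 (Power analysis); 50 per arm (Trial design); 3 follow-up time points and completers only (Primary analysis).

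**Inputs not in the article.** The correlation ρ between repeated measurements and the number of measurements m used in the power calculation. Both are inferred below or varied. Sphericity is assumed throughout.

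**Formula.** For the time effect, or for the condition-by-time effect with two groups: λ = f² × n × m / (1 − ρ), df1 = m − 1, df2 = (n − g)(m − 1), where g is the number of groups. Power is the probability that a noncentral F with these parameters exceeds the 5% critical value.

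**Step 1: reproduce 62 / 24 / 10.** Take g = 2, m = 4, ρ = 0.5 and n in equal arms.
- f = 0.15, n = 62: λ = 0.0225 × 62 × 4 / 0.5 = 11.16, df 3 and 180, power 0.801. With n = 60 it is 0.786.
- f = 0.25, n = 24: λ = 0.0625 × 24 × 4 / 0.5 = 12.0, df 3 and 66, power 0.816.
- f = 0.45, n = 10: λ = 0.2025 × 10 × 4 / 0.5 = 16.2, df 3 and 24, power 0.890.

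All three printed figures match exactly. One group with the same m and ρ gives 62 / 24 / 9, so the required n for the small effect is also 62 in a one-group model.

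**Step 2: two-arm model with 100 participants, f = 0.15, ρ = 0.5.**
- m = 4: λ = 0.0225 × 100 × 4 / 0.5 = 18.0, df 3 and 294, power 0.957.
- m = 3: λ = 0.0225 × 100 × 3 / 0.5 = 13.5, df 2 and 196, power 0.914.

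**Step 3: completers-only model (g = 1) with the maximum of 50, f = 0.15.**

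| m | ρ | required n | λ at n = 50 | power at n = 50 |
|---|---|---|---|---|
| 4 | 0.5 | 62 | 9.00 | 0.70 |
| 3 | 0.58 | 62 | 8.04 | 0.71 |
| 3 | 0.5 | 73 | 6.75 | 0.62 |
| 3 | 0.3 | 102 | 4.82 | 0.48 |
| 3 | 0.7 | 45 | 11.25 | 0.85 |

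The first two rows are inputs under which the one-group requirement is 62. The third uses the 3 time points that the article names. The last two show how far the result depends on the unstated correlation. At ρ = 0.7 a sample of 50 would be enough, but the requirement would then be 45 and not the printed 62.

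**Step 4: what 50 can detect.** At ρ = 0.5, the smallest f with 80% power is 0.167 (m = 4) or 0.182 (m = 3). At f = 0.20 power is 0.93 or 0.87, and at f = 0.25 it is 0.99 or 0.98. The printed requirements of 24 and 10 are both below 50.

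**The case against.** The strongest reply is that the power sentence was written for the two-arm test. It speaks of 100 participants, a number that exists only when both arms are in the model, and the printed set of three is matched exactly by a two-group design, with a one-group design differing in the last figure (9 against 10). On that reading no printed number is wrong. This stands. A reader might infer that the calculation is in error, or that 80% power was promised for the completers-only models specifically. The article supports neither: it attaches its power to 100 participants and to no named model. What remains is that the sentence is unqualified while the section headed Primary analysis opens with models to which it does not apply.

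The second reply is that the first-step models have no control group and so cannot establish efficacy. The condition-by-time test does that work. This also stands and limits the consequence. A reader might conclude that the trial as a whole is underpowered for a small effect. This point does not show that.

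The third reply is that the correlation is not given, so any power figure is conditional. That is right, and 0.62 to 0.70 is not a bound, since the range runs from 0.48 to 0.85 over correlations of 0.3 to 0.7 with 3 measurements. But a correlation high enough to rescue 50 participants is not one that yields 62.

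Finally, the authors expect most or all participants to complete the programme, citing 100% completion among 20 beta testers. No survey dropout rate is given, so the shortfall is stated here at full completion only. Losses would widen it by an unknown amount.

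**Conclusion.** The unqualified claim is correct for the models that include both arms and incorrect for the two completers-only primary models at the small effect. At most 50 participants can enter those models, 12 fewer than the article's own 62. Under inputs that give 62, power at f = 0.15 is about 0.70 rather than 0.80. With the 3 named time points and an assumed correlation of 0.5 it is about 0.62. These figures assume sphericity, full completion and no missed surveys.

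The effect is confined to the lower edge of the expected range: detectable f rises from 0.15 to about 0.17 to 0.18, and the claims for moderate and large effects hold. The matter is one of a stated design property applied too widely, worth correcting because it is cheap to correct and bears on how a null within-arm result would be read.

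**What to change.** Restate the Power analysis section by analysis set:
- For the two-arm condition-by-time models, keep the comparison of 62 with 100 participants, and give the number of measurements and the correlation assumed.
- For the models restricted to intervention completers, state that at most 50 participants are analysed, that 62 would be needed for f = 0.15, and that power for that effect is about 0.70 under the inputs behind 62 (about 0.62 with 3 time points and a correlation of 0.5). Claim adequate power there only for moderate and large effects.

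The cost is a few sentences. Enrolment, data collection and the planned analyses do not change. The only consequence is a less favourable power statement for one set of uncontrolled models.

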**Methods:**

A 2-arm pilot randomized controlled trial (RCT) will be conducted by recruiting young adults ages 18–24 who reported vaping at least once per week in the past 30 days and having never smoked cigarettes at baseline. Participants will be recruited via social media ads and be randomly assigned to an intervention arm, which will be the Live Free From E-cigarettes (LIFFE) mobile-based program (*n* = 50), or a waitlist control arm (*n* = 50). The primary outcomes are biochemically verified 7-day point prevalence abstinence for nicotine vaping, vaping reduction, and smoking susceptibility. Outcomes are measured at 2-, 4-, and 8-weeks after randomization.

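### The power statement holds for an interaction effect of f = 0.15, but does not show that 100 participants can detect a small difference between the arms, and it does not cover abstinence

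*Protocol article*

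**What the plan says.** The Power analysis section states the settings: "Power analyses were performed with power = 0.8 and alpha = 0.05", for "small (f = 0.15), moderate (f = 0.25), and large (f = 0.45) effect sizes". It concludes that with 100 participants "we are adequately powered to detect small (*n* = 62), moderate (*n* = 24), and large (*n* = 10) effects", and adds: "We anticipate small to medium effects based on previous studies using PNF". It does not name the test, the number of measurements, the correlation between them or a dropout rate.

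The Trial design section has participants "randomized to the active intervention arm (*n* = 50) or to a waitlist-control arm (*n* = 50". The Primary analysis section tests vaping frequency and smoking susceptibility by repeated measures ANOVA "across 3 time points (2-, 4-, and 8-weeks post-randomization", and then asks whether any changes "are the result of the interaction between the condition and time". Abstinence is compared between arms by logistic regression. The Abstract lists all three as primary: "The primary outcomes are biochemically verified 7-day point prevalence abstinence for nicotine vaping, vaping reduction, and smoking susceptibility".

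**The concern.** A reader will take the power statement to mean that the trial can detect a small difference between LIFFE and the waitlist. Cohen's f for an interaction is a different quantity. It measures how much the arm difference varies over time, and the labels small and moderate on that scale do not correspond to small and moderate arm differences.

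The article gives efficacy as its primary aim and foresees a larger trial after this pilot. If the result is null and the paper says that the trial was adequately powered for small effects, that result may be taken as evidence that LIFFE does not work, although a difference of 0.2 to 0.3 SD would probably have been missed.

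**Working it through.** **Inputs from the article.** Power 0.80; alpha 0.05; f = 0.15, 0.25, 0.45; stated n = 62, 24, 10; two arms of 50; condition-by-time interaction for the continuous outcomes; logistic regression for abstinence.

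**Assumptions (not in the article).** Number of measurements m, correlation ρ between measurements (0.5, range 0.3 to 0.7), sphericity, and the control abstinence rates.

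**1. Reproducing the stated n.** For the interaction with k = 2 arms, the noncentrality is λ = f²·N·m/(1−ρ), with (k−1)(m−1) and (N−k)(m−1) degrees of freedom. With m = 4 and ρ = 0.5:

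| f | N | λ | Power |
|---|---|---|---|
| 0.15 | 62 | 0.0225 × 62 × 4 / 0.5 = 11.16 | 80% |
| 0.25 | 24 | 0.0625 × 24 × 4 / 0.5 = 12.0 | 82% |
| 0.45 | 10 | 0.2025 × 10 × 4 / 0.5 = 16.2 | 89% |

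Each N is the smallest even total that reaches 80%, so the trio matches exactly. This match is not unique. With m = 3 the same trio appears at ρ of about 0.58 to 0.59; at ρ = 0.5, m = 3 gives 74, 28 and 10. A one-group time effect with m = 4 and ρ = 0.5 gives 62, 24 and 9.

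**2. Converting f to an arm difference.** In SD units, f² is the mean over time of [(arm difference at time t − its time average)/2]². Take differences of 0, d, d, d at baseline and weeks 2, 4 and 8. The time average is 0.75d and the halved deviations are −0.375d and three times 0.125d. Then f² = (0.140625 + 3 × 0.015625)d²/4 = 0.046875d², so f = 0.2165d.

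- f = 0.15 gives d = 0.15/0.2165 = 0.69 SD.
- f = 0.25 gives d = 1.15 SD.
- Other patterns give a similar answer at f = 0.15: about 0.80 to 0.81 SD at week 8 if the difference grows linearly, and a peak of 0.72 SD if it fades as 0, d, d/2, 0.

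**3. Interaction power for arm differences, N = 100, m = 4, no dropout.**

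| Sustained d | f | λ at ρ = 0.5 | Power at ρ = 0.5 | Power at ρ = 0.3 / 0.7 |
|---|---|---|---|---|
| 0.2 SD | 0.043 | 1.5 | 15% | 12% / 23% |
| 0.3 SD | 0.065 | 3.375 | 30% | 22% / 48% |
| 0.5 SD | 0.108 | 9.375 | 72% | 56% / 92% |

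At ρ = 0.5, 80% power is reached at f = 0.1175, so d = 0.1175/0.2165 = 0.54 SD (0.64 SD at ρ = 0.3, 0.42 SD at ρ = 0.7). With 80 analysed and ρ = 0.5 it is 0.61 SD.

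**4. If only the three follow-ups enter the model.** A constant difference d, d, d has no deviation from its time average, so f = 0. The interaction then cannot detect a sustained benefit at any N. The difference falls to the main effect of condition, where λ = f²·N·m/(1+(m−1)ρ). At f = 0.15, N = 100 and m = 3, its power is 44% at ρ = 0.5 (53% at 0.3, 38% at 0.7).

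**5. Abstinence.** Cohen's f for a repeated measures ANOVA says nothing about a comparison of two proportions. With 50 per arm, two-sided 0.05 and assumed control rates, 80% power needs roughly 5% versus 24–25%, 10% versus 33%, or 20% versus 46%. A contrast of 10% versus 20% has about 30% power.

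**The case against.** The strongest reply is that the article states its f values and that 100 participants are ample for them. That is correct: at f = 0.15 on the interaction scale, N = 100 gives 96% power with four measurements and 91% with three, at correlation 0.5. What fails is the step from that effect to a small difference between arms.

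Four stronger readings are tempting, and the article does not support them.

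- *The calculation used four time points although three are planned.* This is only inferred. The article states neither m nor ρ, and three measurements at a correlation of 0.58 to 0.59, a plausible value, give the same three numbers.
- *The trial cannot detect the small to medium effects that it expects.* This is too flat. At 0.5 SD the interaction has 72% power at correlation 0.5 and 92% at 0.7, and the article does not give the metric of the effects expected from earlier work. The shortfall is clear at 0.2 to 0.3 SD.
- *0.69 SD is the limit of what the trial can detect.* It is the effect labelled small. The 80% limit at N = 100 is about 0.54 SD.
- *There is no room for dropout.* No rate is stated, but at the article's own f the gap between 62 and 100 leaves ample room.

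A condensed article may also leave power inputs and an abstinence calculation to the full protocol. Their absence alone would not be a finding. They matter here because the article makes an unqualified claim of adequate power in a trial with three primary outcomes. The pilot label is a good reason to keep N, but not a reason to keep the claim.

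**Conclusion.** The stated n are right for their own f, and the conclusion drawn from them is wrong as worded. With baseline included and a sustained effect, 0.15 on the interaction scale is 0.69 SD between arms. With 100 analysed, the interaction has 15% to 30% power at 0.2 to 0.3 SD and reaches 80% at about 0.54 SD. This rests on a correlation of 0.5, sphericity and full follow-up; over correlations of 0.3 to 0.7 the detectable difference runs from 0.64 to 0.42 SD, so no value in that range brings 0.2 or 0.3 SD within reach. If the model holds only the three follow-ups named in the Primary analysis section, a constant arm difference produces no interaction at all. For abstinence the power statement gives no information, and the detectable contrast is large.

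**What to change.** Keep N = 100 and rewrite the Power analysis section:

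1. Withdraw the claim of adequate power for small effects, or limit it expressly to an interaction effect of f = 0.15.
2. State the test, the number of measurements, the correlation and the attrition assumed, and say whether baseline is one of the measurements in the primary model.
3. Give the detectable between-arm difference for the planned condition-by-time repeated measures ANOVA with baseline included: at correlation 0.5, about 0.54 SD with 100 analysed and about 0.61 SD with 80.
4. Give the detectable abstinence contrast at 50 per arm, for example roughly 10% versus 33%, and state the assumed control rate.

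A baseline-adjusted comparison would detect less: about 0.36 SD for the mean of the three follow-ups and 0.49 SD for a single week, at correlation 0.5 without dropout. Quote these figures only if the Primary analysis section is changed to that method; otherwise the power statement and the analysis would disagree.

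The cost is a text change with no extra participants. The downside is that the stated power becomes less favourable.

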### Ethics approval

The study protocol was approved by the Institutional Review Board at the University of Southern California (USC IRB). The protocol is registered with ClinicalTrials.gov (protocol # NCT06129123). Any amendments to the protocol will need to be approved by the USC IRB prior to implementing the changes.

### Data monitoring

The Principal Investigator (PI) will be responsible for data safeguarding by implementing the Data and Safety Monitoring Plan. This study will collect data which includes the following information: participant email addresses, phone numbers, and first name. These identifiers are necessary to notify and contact participants about the survey and to send follow-up reminders during the data collection period. PIN codes connecting this identifiable information with confidential data will be randomly assigned to the sample data. The sample data will not be stored in the same database as the survey data, which will be collected by Qualtrics. Thus, survey data will not contain any identifying information. The PIN code is stored together with the answers given by participants. Access to study data will be limited only to the PI and a limited number of study personnel. All individual linkages to data after a participant ends their participation in the study or at the end of the project period will be destroyed.

The PI and the study team will make the determination between adverse events and serious adverse events. All serious adverse events, adverse events, and unanticipated problems will be managed consistent with guidelines set forth by the USC IRB. Any significant adverse events will be reported within 48 h, and all adverse events will be reported on the annual status report in compliance with federal regulations. Participants will be informed that they should contact the PI and/or the USC IRB to report complaints or adverse events.

A Data and Safety Monitoring Board (DSMB) consisting of three members will be created as an independent body with the responsibility of ensuring that the safety of study participants is protected. For example, the DSMB will review any proposed amendments to the study protocol, complete expedited monitoring of all serious adverse events, perform ongoing monitoring of drop-outs and non-serious adverse events, determine whether study procedures should be altered or the study should be paused or terminate for reasons related to the safety of study subjects, and execute periodic review of the completeness and validity of data to be used for analysis of safety and efficacy. The DSMB will also confirm subject privacy and research data confidentiality.

## Discussion

This is the first clinical trial of a mobile-based vaping intervention combined with smoking prevention content for young adults. As vaping among young adults and this risk for future smoking continue to be a concern for tobacco control efforts, this study is timely and urgently needed. LIFFE was developed based on evidence from interventions that addressed other substance use behaviors [25, 30] in young adults, best practices recommended for the treatment of nicotine use and dependence [31], and qualitative work outlining what young adults felt they believed would be essential for vaping cessation or reduction and smoking uptake prevention [24]. Results will be disseminated via publication, scientific meetings, and social media platforms for public viewing.

As technology continues to evolve, it will be important to remain well-informed of ways to utilize available technological platforms to develop innovative strategies to engage a diverse population of young adults in vaping cessation and reduction efforts [45]. A text messaging program was found to be effective for promoting abstinence among young adults who vape [20]. Participants received nine weeks of text messages and had to report interest in quitting vaping in the next 30 days. In mental and behavioral health treatments, longer-term as well as shorter-term treatment options are available, giving patients the opportunity to select treatments that best meet their needs and preferences. Patients who prefer briefer options may find LIFFE to be most feasible. Further, LIFFE was designed to appeal to all young adults who vape, including those who may have never considered quitting or reducing their vaping. This brief model offers an excellent opportunity for these young adults to engage in a “foot-in-the-door” approach or entry to practicing healthy behavior change. Future research should continue to prioritize exploring alternative options or diverse channels to identify the most effective platforms that appeal to diverse youth populations.

